**Figure 1 F1:**
[figure not shown]
Schematic of Overall Design for TeamCare-PCN Study.

**Figure 2 F2:**
[figure not shown]
TeamCare-PCN Study Procedures.

Our decision to employ a pragmatic approach was based on a number of factors. First, the efficacy of the intervention has been established [28,29], so it is important that external validity now be accorded similar attention to the usual concerns related to internal validity [33-35]. Second, various forms of case-management have generally shown to be effective in improving quality of care for patients with diabetes [36]. Third, the effectiveness, applicability, and feasibility of the intervention have only been established in the urban managed care setting in the US [29]. Testing this intervention in a Canadian primary care setting is crucial to claim its effectiveness and applicability to the Canadian context. Finally, limitations in the available scientific information often impede the efforts of health policy makers and care providers in making evidence-informed policies for new and existing health technologies and interventions [33]. This results in allocating scarce healthcare dollars to interventions where the effectiveness and cost-effectiveness in routine clinical settings have not been evaluated [34,35,37]. While an economic evaluation of the original TEAM Care intervention was undertaken from the perspective of a US managed care organization provider [30], it is important to adopt a pragmatic approach to evaluate the effectiveness and cost-effectiveness of the TeamCare-PCN intervention in the Canadian context, and make this information available to support local health policy making and resource allocation.

### Hypotheses

We hypothesize the TeamCare-PCN intervention will reduce depressive symptoms, increase achievements of targets for cardio-metabolic measures, improve lifestyle behaviors, and be cost-effective. Furthermore, we anticipate this intervention will be acceptable and feasibly implemented in the PCN environment.

### Setting and population

TeamCare-PCN will be conducted in collaboration with four PCN in non-metro Alberta. A PCN is akin to the “medical home” concept [38], established as a network of primary care physicians in a given geographical area. Through the provincial Primary Care Initiative framework, funding is provided based on an approved business plan for the provision of primary care services to the local population. Each network has the flexibility to develop programs and to provide services in a way that works locally to meet the specific needs of patients. Funding may be used to establish central PCN office/clinic space, and hire allied health professionals, such as nurses, dieticians, pharmacists, or therapists. At the time of the launch of this study, there were 40 PCNs operating throughout Alberta, with about 80% of eligible family physicians working within a PCN. We elected to partner with PCNs outside of the larger metro centers because these cities already have greater access to specialist care as well as more established regional diabetes care and management programs than the non-metro PCNs. Collectively, the four participating study PCNs represent 140 general physicians and approximately 180,000 patients, with an estimated 10,000 patients with type 2 diabetes.

### Eligibility criteria

Inclusion Criteria:

 · Have type 2 diabetes and under the care of a PCN family physician and be

 · 18 years of age or older and

 · Score > =10 on the PHQ-9 [29,39,40] and

 · Speak English and have adequate hearing to complete telephone interviews and

 · Be willing and able to provide written informed consent to participate

Exclusion Criteria:

 · Severe and/or terminal physical illness (e.g. heart disease, renal failure, cancer, major organ failure) or

 · Serious and/or severe mental or psychiatric illness (e.g. bi-polar disorder or schizophrenia, use of anti-psychotic or mood stabilizer medication, or cared for by a psychiatrist); patients taking anti-depressants or receiving supportive psychotherapy from non-psychiatrists would be eligible or

 · Pregnant or breastfeeding or

 · Live in long-term care facility or

 · Already participating in other clinical trials

### Recruitment and allocation

Recruiting participants into TeamCare-PCN involves three steps. * First *, a screening survey accompanied with an endorsement letter from the PCNs will be mailed out to all patients with type 2 diabetes on the PCNs’ diabetes registries. This survey asks about age, the ability to read and speak English, having type 2 diabetes, length of time since diagnosis, and screens for depressive symptoms. * Second *, after potential participants have completed and returned the screening survey, PCN staff will contact eligible participants to confirm all eligibility criteria and if the participant is willing to participate, and schedule a baseline assessment visit. * Third *, during the baseline visit, the Care Manager (CM) will confirm eligibility, explain the intervention, provide an intervention-specific information letter and obtain a signed written informed consent from the patient to participate in the study.

Participants will be allocated to study groups using a previously successful “on-off” group assignment method (Figure 1) [39,41,42]. Eligible and consenting respondents who book for a baseline assessment with the CM during month 1 will be allocated to the intervention arm (ON-group). Those who book the baseline assessment in month 2 will be allocated to the usual care arm (OFF-group). This allocation process will continue until the target sample size is recruited. This method has been used in many quality improvement studies, reliably leads to balance in measured [and unmeasured] patient characteristics [39,41,42], and meets study design criteria for internal validity sufficient to permit inclusion in the Cochrane Collaborations’ Effective Practice and Organization of Care (EPOC) systematic reviews [40]. Because all four sites are involved in both “on” and “off” phases, this particular study design also balances case mix and controls for Hawthorne or volunteer effects, as well as issues related to “institutional learning” over time [39,40,42].

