#### Patient management

Patients entering the intervention will have a two-hour baseline appointment with the CM. This first visit will include a bio-psychosocial semi-structured assessment (reviewing medical history, previous treatments for depression and diabetes), patient education, potential treatment options (anti-depressant medications and/or psychotherapy) and developing an overall individualized care plan.

As mentioned, the intervention will consist of 3 phases; the first focusing on depression management, the second on cardio-metabolic diabetes management, and the third on general lifestyle modifications. A treat-to-target/stepped care approach will be used at each phase of the intervention. Recommended treatments have been based on algorithms that were developed in collaboration with the PCNs by compiling various guidelines and sources, such as extant clinical practice guidelines and consulting experts in the field. The CM will actively follow-up by telephone or in person one to two times per month to re-assess symptoms, and assist and support patients in achieving treatment goals. The CM will also have weekly meetings with the consulting specialists to review new cases and patient progress, and then communicate team treatment recommendations to the primary care physician.

The depression management phase (Phase 1) will involve the use of anti-depressant medications and/or referral for psychotherapy, as determined by the CM and the family physician (with study psychiatrist consultation as needed by the CM), tailored to each patient. A two-day training session for CM and consultant specialists was planned at the beginning of the project, with an annual one-day booster session The CM will be given basic training in three psychotherapeutic techniques during this phase: problem-solving therapy [46-49], behavioral activation [50-54], and motivational interviewing [55-57]. Direct referral to the care of a psychiatrist will occur only on failure of two separate trials of anti-depressants, or one trial of anti-depressant in combination with psychotherapy. Once patients have reached remission, the CM and patient work together towards a relapse prevention plan to help the patient identify when and where to seek help with future depressive symptoms or renewed problems for disease control. The CM will continue to work with patient through Phases 2 and 3 of the intervention.

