### Outcome measures

To assess the effectiveness (“E” in RE-AIM) of TeamCare-PCN, we will use two primary outcome measures. First, given that we selected patients on the basis of depressive symptoms, our primary depression-related outcome will be the PHQ-9 scores at 12 months. Second, a global measure of patient-centered improvement (the scaled marginal model, see Analysis below) based on the combination of chronic disease-related clinical outcomes. All outcomes will be measured in all participants (i.e., both groups) at baseline, 6, and 12 months. We will secondarily evaluate process indicators for care received, as well as a host of patient-reported outcome measures to determine the overall effectiveness of the TeamCare-PCN intervention.

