### Data analysis

As the initial focus of the intervention is on the management of depressive symptoms, we have considered the PHQ-9 as a main primary outcome, and will assess changes in PHQ-9 scores over 12-months between groups, adjusting for baseline PHQ-9 score, using a mixed effects multivariate model. For our second primary outcome of improvements in global disease control, we will employ a multivariate model that jointly tests the changes in multiple clinical outcomes, namely A1c, LDL cholesterol and systolic blood pressure [29]. Using the same analytic approach as in the recently published RCT of this intervention, we will apply a scaled marginal model [29,75] to simultaneously compare the change in these continuous outcomes at 12 months, adjusting for the baseline status for each variable. This approach scales the changes in each outcome by its standard errors, and thus the coefficients can be directly interpreted as effect sizes [29]. In either primary outcome analyses, the models will be estimated iteratively and the potential correlations among and between outcomes within individuals will be handled using generalized-estimating equation (GEE) models for each outcome [75].

We will also compare the study arms based on the proportion of subjects who achieved a remission of depression (i.e., PHQ-9 < 10 for 3 consecutive months) and the proportion of patients who achieve a clinically important change in the outcomes (that is, achieving a reduction of 5 points on the PHQ-9 [44] or a 10% or greater improvement over baseline values for A1C, LDL cholesterol and SBP at 12 months) [59,60], using generalized estimating equations and multivariable logistic regression models. This approach will allow us to present and interpret all outcomes in terms of absolute differences and a number-needed-to-treat [76].

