### Ethics and funding considerations

All patient participants will receive information about the study and the opportunity to ask any questions. Written informed consent will be obtained from participants prior to obtaining any study measurements. Ethics approval for the study and its evaluation has already been granted from the Health Research Ethics Board (HREB #PRO00012663) at the University of Alberta. The broader evaluation component of this study was also submitted to the HREB for review. However, the Board deemed this component of the study as evaluation and not research; it was deemed to not require ethics review and approval. Regardless, the requirements outlined in the Tri-Council Policy Statement: Ethical Conduct of Research Involving Humans [87] will be followed in this study. Verbal informed consent from participants will be sought prior to any evaluation activities.

The funding for this study is from a contract from the provincial government (Alberta Health and Wellness) to the Alliance for Canadian Health Outcomes Research for Diabetes (ACHORD) Group. The funding source had no role in the design of the study and will have no role in the conduct, analysis or reporting of the study, nor access to the data.

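### Self-reported measures taken at the baseline visit follow allocation and the care manager's explanation of the intervention, and the plan does not say which PHQ-9 the primary model adjusts for

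*Protocol article*

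**What the plan says.** All references are to the protocol article.

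- **When the arm is fixed** (Recruitment and allocation): the rule for the opening month is "Eligible and consenting respondents who book for a baseline assessment with the CM during month 1 will be allocated to the intervention arm (ON-group", whereas the rule for the next month is "Those who book the baseline assessment in month 2 will be allocated to the usual care arm (OFF-group". Allocation is therefore settled before the visit takes place.
- **What happens at the visit** (same section): "the Care Manager (CM) will confirm eligibility, explain the intervention, provide an intervention-specific information letter and obtain a signed written informed consent".
- **When measurement may start** (Ethics and funding considerations): "Written informed consent will be obtained from participants prior to obtaining any study measurements".
- **What else an intervention patient's first visit holds** (Patient management): "Patients entering the intervention will have a two-hour baseline appointment with the CM". The section lists a psychosocial assessment, education, treatment options and a care plan as its content. Under Usual care, the other arm gets no active care-manager support.
- **What is measured** (Outcome measures): "All outcomes will be measured in all participants (i.e., both groups) at baseline, 6, and 12 months".
- **How baseline enters the primary analyses** (Data analysis): the PHQ-9 analysis is described as "adjusting for baseline PHQ-9 score, using a mixed effects multivariate model". The disease-control analysis will "simultaneously compare the change in these continuous outcomes at 12 months, adjusting for the baseline status for each variable".
- **Earlier PHQ information** (Overall study design; Recruitment and allocation): depressive symptoms are also screened at first cohort contact and in the mailed survey, before any visit is booked.
- **Masking** (Data management): investigators, research staff and analysts are masked. Patients and care managers are not mentioned.

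**The concern.** A baseline covariate does its job only if the treatment arm cannot have influenced it. The PHQ-9 and the patient-reported scales are self-reports. Someone who expects a nurse-led programme, or has just been through a long assessment and education session, may answer differently from someone who knows that nothing extra is coming. The direction is open. Relief in the intervention arm, or disappointment in usual care, would work against the intervention. Fuller symptom reporting after probing in the intervention arm would work in its favour.

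This matters more here than in a randomised trial. The Data analysis section itself calls the allocation non-random and looks to covariate adjustment to deal with imbalance, including covariates picked because they differ at baseline. A self-report already shifted by knowledge of the arm is a poor tool for that purpose. Baseline PHQ-9 is also the reference for the 5-point-reduction responder analysis, where a shift enters in full.

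**Working it through.** **Step 1: order of events.** The sections, set side by side, give this sequence:

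1. Screening PHQ, before booking.
2. Visit booked; the booking month fixes the arm.
3. Baseline visit: eligibility confirmed, intervention explained, letter given, written consent signed.
4. Study measurements, which may not precede consent.

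Steps 2 and 3 come from Recruitment and allocation, and the constraint on step 4 from Ethics and funding considerations. Any PHQ-9 or survey taken at the visit therefore falls after allocation and after the explanation. For intervention patients, nothing in the text places it before the education and care planning that share the appointment.

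**Step 2: which outcomes can move.** A1c and LDL come from point-of-care devices on capillary blood (Chronic disease-related clinical outcomes). Information heard earlier in the same visit can hardly alter them. Systolic pressure might react slightly. The PHQ-9 and the scales under Patient-reported outcomes are the exposed measures.

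**Step 3: which PHQ-9.** Data analysis refers only to the baseline score. If that is the visit score, step 1 applies. If it is the screening score, it precedes allocation and the PHQ-9 model is not affected in this way. The text does not settle it.

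**Step 4: illustrative size.** The plan states no figure on this point, so there is none to reproduce.

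Inputs from Sample size and power considerations: repeated-measures correlation r = 0.6; target difference 5 points. Assumptions, not from the documents: equal SDs at baseline and 12 months; a shift d (intervention minus usual care) in the recorded baseline that does not carry into the 12-month score; 12-month scores observed.

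- Slope: β = r × (SD at 12 months / SD at baseline) = 0.6 × 1 = 0.6.
- Adjusted difference = (difference in 12-month means) − β × (difference in recorded baseline means), so bias = −β × d. Analysing change with the same baseline covariate gives the same treatment coefficient.
- Unadjusted change: bias = −d.

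| Assumed shift d | Bias in adjusted difference, absolute | Share of 5 points | Bias in unadjusted change, absolute | Share of 5 points |
|---|---|---|---|---|
| 0.5 | 0.6 × 0.5 = 0.3 | 6% | 0.5 | 10% |
| 1 | 0.6 × 1 = 0.6 | 12% | 1 | 20% |
| 2 | 0.6 × 2 = 1.2 | 24% | 2 | 40% |

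A simulation (4,000 runs, 60 per arm, assumed SD 5, d = +1) gave a mean bias of −0.57, close to the −0.6 from the formula. Because higher PHQ-9 scores are worse, a positive d flatters the intervention and a negative d counts against it.

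**The case against.** The strongest reply is that the article does not fix as much as it seems to.

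- **Disclosure is inferred.** No sentence says that patients learn their arm before they are measured. The letter may be specific to this study as opposed to the wider cohort survey, and the same step is described for recruits of both arms. This stands: knowledge of the arm is plausible, not stated. It is hard to avoid, though, for an intervention patient measured after education or care planning, and no patient masking is described.
- **The PHQ-9 may already be a pre-allocation score.** The Depression-related outcome section ties participants' scores to eligibility, which fits the screening value. This also stands, and it rules out saying that baseline PHQ-9 is measured only after the explanation. Against it, the visit is called a baseline assessment and all outcomes are to be measured at baseline in both groups, which makes the visit score the more natural reading.
- **Eligibility is confirmed first.** If the PHQ-9 were repeated at that point it would precede the explanation. It would then also precede written consent, which the ethics section does not allow for a study measurement.
- **The detail may lie elsewhere.** The study-procedures figure is not shown and may give the order. That is a reason for caution, but the stated text, if followed, leaves self-report exposed.

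A reader might also infer that both primary analyses are compromised because both adjust for baseline. The documents do not support that: the second uses A1c, LDL and systolic pressure, for which the mechanism is absent or slight.

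**Conclusion.** The point holds in a limited form. As written, self-reported measures taken at the baseline visit come after allocation, after the care manager has explained the intervention, and after consent. The protocol does not identify the baseline PHQ-9 in the first primary model. The exposure covers the PHQ-9 and the other patient-reported scales, not the cardio-metabolic outcome.

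Neither the existence, the size nor the direction of a shift can be established from the documents. The range of 0.3 to 1.2 points describes assumed shifts of 0.5 to 2 points under a slope of 0.6 and equal SDs; it is not an estimate for this trial. Under last-observation-carried-forward, a patient whose baseline is carried forward shows zero change whatever the shift, so with similar attrition in the two arms the bias would be diluted. If the model uses the screening PHQ-9, the concern falls away for that model and remains for the other self-reports. This is a worthwhile and inexpensive improvement, not a flaw that invalidates the trial.

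**What to change.** 1. **Use one visit order in both arms.** Consent to assessment with a neutral letter that does not reveal the arm; then self-completed PHQ-9 and survey; only then arm-specific information and care-manager content. The clinical measurements can conveniently be taken with the self-report, although little depends on this.
2. **Name the baseline.** State in Data analysis whether the covariate is the visit PHQ-9 or the screening PHQ-9.
3. **If it is the visit score, add a sensitivity analysis** that replaces it with the screening PHQ-9 obtained before booking. For anyone enrolled before the visit order changes, this is the only available check.

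**Cost.** A consent-letter amendment for the ethics board, which has already approved the study, and a short visit script. No extra visit, staff or measurement is needed. If recruitment is under way, introduce the new order at the start of a full on-off pair of months so that both arms change together. The screening score is older and truncated at 10, so it adjusts slightly less efficiently. That is acceptable in a sensitivity analysis.

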**Methods/design:**

We initiated the TeamCare model in four Primary Care Networks in Northern Alberta. The intervention involves a nurse care manager guiding patient-centered care with family physicians and consultant physician specialists to monitor progress and develop tailored care plans. Patients eligible for the intervention will be identified using the Patient Health Questionnaire-9 as a screen for depressive symptoms. Care managers will then guide patients through three phases: 1) improving depressive symptoms, 2) improving blood glucose, blood pressure and cholesterol, and 3) improving lifestyle behaviors. We will employ the RE-AIM framework for a comprehensive and mixed-methods approach to our evaluation. Effectiveness will be assessed using a controlled “on-off” trial design, whereby eligible patients would be alternately enrolled in the TeamCare intervention or usual care on a monthly basis. All patients will be assessed at baseline, 6 and 12 months. Our primary analyses will be based on changes in two outcomes: depressive symptoms, and a multivariable, scaled marginal model for the combined outcome of global disease control (i.e., A1c, systolic blood pressure, LDL cholesterol). Our planned enrolment of 168 patients will provide greater than 80% power to observe clinically important improvements in all measured outcomes. Direct costing of all intervention components and measurement of all health care utilization using linked administrative databases will be used to determine the cost-effectiveness of the intervention relative to usual care.

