## Methods

### Overall study design

We will evaluate the effectiveness (i.e., the “E” in RE-AIM) of the TeamCare-PCN intervention using a controlled pragmatic trial design. We have implemented a variant of a practical design referred to as “cohort multiple RCT” (Figure 1) [32]. Patients with type 2 diabetes registered at PCNs will be invited to participate in an ongoing, annual survey as part of a larger Alberta’s Caring for Diabetes (ABCD) Cohort Study. Initial contact with cohort participants includes the administration of the Patient Health Questionnaire, a brief depression screening survey, and if positive for depressive symptoms, respondents will be invited to participate in the TeamCare-PCN study. We will allocate eligible participants to the intervention and usual care arms using an “on-off” time series (Figure 1); all participants will be assessed at baseline, 6 and 12 months.

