#### Chronic disease-related clinical outcomes

Clinical outcome measures include systolic blood pressure (SBP), LDL cholesterol and A1c, demonstrated by achievement of targets or significant improvements as indicated with a 10% improvement over baseline [59,60]. These outcomes will be measured using point-of-care devices that we have standardized and placed in each PCN. Capillary blood samples will be collected from participants to assess A1c and lipid profile. Cardiovascular (blood pressure and resting heart rate) and anthropometric (weight, height, and waist circumference) measurements will also be assessed at clinic visits. Regular, monthly quality assurance checks will be conducted on the point-of-care devices, validated against central laboratory measurements.

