### Data management

The depression and medical outcome measures will be entered into a clinical management tracking system as part of the TeamCare-PCN intervention. The data collected in the survey and through clinical measurement will be entered into centralized, web-accessible databases. These study databases will be housed on secure servers in the research offices at the University of Alberta. Double data entry will be conducted and research staff will remain masked to allocation status at all times. Once the study is completed, all data will be exported and merged, based on individually assigned study ID numbers, to form an analyzable dataset. Investigators, research assistants, and analysts will be masked to allocation status at all times.

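### If the four PCNs share one ON/OFF calendar, on-schedule visits never place both arms in the same month, so month-to-month shifts in A1c, LDL and SBP add variance that the stated analysis does not count

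*Protocol article*

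**What the plan says.** The abstract says that "eligible patients would be alternately enrolled in the TeamCare intervention or usual care on a monthly basis". Recruitment and allocation gives the rule: "Eligible and consenting respondents who book for a baseline assessment with the CM during month 1 will be allocated to the intervention arm (ON-group". For the following month, "Those who book the baseline assessment in month 2 will be allocated to the usual care arm (OFF-group". The section adds: "This allocation process will continue until the target sample size is recruited". Only one sequence of months is described for the four PCNs. Overall study design adds that "all participants will be assessed at baseline, 6 and 12 months".

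A1c, LDL and SBP form the second primary outcome. They are measured with point-of-care devices placed in each PCN, and under Chronic disease-related clinical outcomes "Regular, monthly quality assurance checks will be conducted on the point-of-care devices, validated against central laboratory measurements".

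Because every site takes part in both phases, Recruitment and allocation says that "this particular study design also balances case mix and controls for Hawthorne or volunteer effects" and for institutional learning over time. Data analysis allows adjustment for PCN site and for baseline differences between the groups; it names no month or period term. Data management says that "research staff will remain masked to allocation status at all times", and says the same of investigators and analysts.

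**The concern.** Having every site in both phases balances sites. It does not balance calendar months if the sites switch together, because each month then holds one arm only. Under any shared calendar, the 12-month visits in a given month come from one enrolment month and so from one arm. Here the 6- and 12-month intervals are also multiples of the cycle, so baseline and 6-month visits made in that month belong to the same arm too. A device's results in a given month then contain nothing from the other arm.

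Anything that moves A1c, LDL or SBP readings in a particular month at all sites, such as a recalibration after a monthly check or a holiday month, therefore enters the arm comparison. A model with patient-level errors, site and baseline covariates leaves that variation out of its standard error, so the test of the second primary outcome would reject too often under the null.

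There is a second, smaller issue. A baseline date that falls in the allocated month tells anyone who knows the rota which arm the patient is in, which sits badly with masking throughout.

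**Working it through.** The protocol gives no figure on this point, so there is none to reproduce.

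**Inputs from the protocol.** Month 1 ON and month 2 OFF, repeating; visits at 0, 6 and 12 months; 4 PCNs; 168 patients planned and 120 (60 per arm) needed for analysis (Sample size and power considerations).

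**Assumptions.** Month shifts are independent with SD τ = 0.1, 0.2 or 0.3 of an outcome SD. The analysed change has SD 1. Recruitment is even over 12 or 24 months, site sizes are equal, and visits are on time. The protocol gives neither a shift size nor a recruitment period.

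**1. Parity.** For enrolment month m and visit time f = 0, 6 or 12, (m + f) mod 2 = m mod 2. ON patients fall in months 1/7/13, 3/9/15 and so on; OFF patients fall in 2/8/14, 4/10/16 and so on. On the nominal schedule 100% of visits fall in own-arm months.

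**2. How exact this is.** Let visits vary uniformly by ±w days, with a month of M = 365.25/12 = 30.44 days. The share of follow-up visits in own-arm months is 1 − w/(2M) for w up to M:
- ±3 days: 95%
- ±7 days: 89%
- ±14 days: 77%
- ±21 days: 65%
- ±30 days: 51%, so the pattern is gone.

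If allocation follows the day the booking is made, a uniform lag of 0 to L days before the baseline visit gives the same formula with L for w: 89%, 77% and 51% for 7, 14 and 30 days.

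**3. Added variance.** A patient enrolled in month m carries shift(m + 12) − shift(m) in the 12-month change.
- 12 months of recruitment: 6 ON and 6 OFF months involve 24 distinct month shifts, each with weight 1/6. V = 24τ²/36 = 0.667τ², so the SD is 0.82τ.
- 24 months: shifts in months 13 to 24 enter once as follow-up and once as baseline within the same arm, and cancel. That leaves 24 shifts with weight 1/12. V = 24τ²/144 = 0.167τ², so the SD is 0.41τ.
- Shifts independent by site: divide V by 4.

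The patient-level variance of the arm difference is 4/168 = 0.0238 (SE 0.154) or 4/120 = 0.0333 (SE 0.183). The true error of a nominal 5% test is 2[1 − Φ(1.96 × SE/√(SE² + V))].

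Example (12 months, 168 patients, common shifts, τ = 0.2): V = 0.667 × 0.04 = 0.0267; √(0.0238 + 0.0267) = 0.225; 1.96 × 0.154/0.225 = 1.35; error about 18%.

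| Recruitment | Patients | Shifts | τ = 0.1 | τ = 0.2 | τ = 0.3 |
|---|---|---|---|---|---|
| 12 months | 168 | common to sites | 8% | 18% | 30% |
| 12 months | 168 | independent by site | 6% | 8% | 12% |
| 12 months | 120 | common to sites | 7% | 14% | 24% |
| 24 months | 168 | common to sites | 6% | 8% | 12% |
| 24 months | 168 | independent by site | 5% | 6% | 7% |
| 24 months | 120 | common to sites | 6% | 7% | 10% |

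**4. Sensitivity to baseline adjustment.** The planned model adjusts for baseline, so baseline shifts may count for less than in a raw change. If they counted for nothing, V = 2τ²/6 for 12 months of recruitment. With 120 patients and common shifts the error would be 6.2%, 9.8% and 15.5%.

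**The case against.** Much of the case on the other side stands.

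- **The shared calendar is read, not stated.** The text speaks of month 1 and month 2 without saying that the PCNs start together, and the schematic is not available here. If the sites launched in different months, the rota may already be partly staggered. A single calendar is the natural reading, but the point is conditional on it.
- **Visits need not be on time.** No window is given, and booking in a month may mean the day the booking is made. A reader might infer that the arms are always measured in opposite months; that holds only on the nominal schedule.
- **Shifts may be local and small.** Each PCN has its own device, standardised and checked monthly against the central laboratory, which should limit shifts. Those confined to one site matter much less, as the table shows.
- **It is not a fixed bias.** A reader might infer that device shifts keep favouring one arm. Alternation spreads drift and independent monthly shifts over both arms. A directional bias would need a shift tied to odd or even months, and nothing in the protocol suggests one.
- **It is not beyond analysis.** A reader might infer that no model can deal with month. Fixed month effects are aliased with arm, but the variance between months can be estimated because each arm spans several months. In a simulation with 12 months of recruitment and common shifts, a test on month-level means held its error at 5.0% to 5.1%. A separate analysis plan could specify this, but it would not bring both arms into the same month.
- **Masking.** Any known on-off rota lets the baseline date reveal the arm, whatever the follow-up interval. Family physicians are told the allocation anyway (Usual care), and the protocol does not say that masked staff see visit dates.

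These points limit the size and certainty of the problem. They do not remove the overlap of arm and month under the calendar as written, or supply a term for month in the stated model.

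**Conclusion.** The point holds in conditional form. On the nominal schedule, and with one calendar for all four PCNs, arm and calendar month coincide at every visit. Variation between months that is common to sites then goes uncounted in the comparison of A1c, LDL and SBP.

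The 30% at the top of the range needs large shifts (0.3 SD) shared by all sites, a 12-month recruitment period, 168 analysed patients and punctual visits. Relaxing any one of these brings the figure down, and with site-specific shifts and 24 months of recruitment the inflation is at most about 2 percentage points.

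The effect is extra variance, not a systematic advantage for one arm, and the device argument does not touch PHQ-9. The masking conflict is real for anyone who knows the rota and sees a baseline date falling in the allocated month. The protocol leaves open whether masked staff see such dates.

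**What to change.** Stagger the calendar so that two PCNs are ON while the other two are OFF. The abstract says that the model has been initiated; if recruitment is already running, apply this to the remaining months. Each staggered recruitment month then holds both arms, a shift common to sites largely cancels, and calendar month can be fitted beside site and arm. If staggering is no longer possible, specify a random month effect or month-level clustering for A1c, LDL and SBP.

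Give masked data staff and analysts study-day numbers in place of visit dates.

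The cost is small: no extra patients or visits, but site-specific rotas must be tracked. Staggering does not remove shifts confined to one site's device in one month. It also does not by itself restore masking, because site and date together would still reveal the arm; withholding the dates deals with that part.
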